### Statistical analysis

Concerning the primary endpoint (overall survival), the log-rank test for univariable testing and Cox regression would be used to compare the long-term prognosis among patients in the extended lymphadenectomy group and the regional lymphadenectomy group in the intention-to-treat population. Secondary endpoints include DFS, survival without recurrence of regional nodal metastases, distant metastasis-free survival, the primary complication within 30 days after surgery (Clavien-Dindo grade > II), and perioperative mortality. Time zero is set as the time of randomization. After enrollment, all patients who have been randomized would be included in the full analysis set (FAS). On the basis of the FAS, patients who meet the inclusion and exclusion criteria (Table 1), are compliant, and do not violate the clinical trial protocol would form the per protocol set (PPS).

**Table 1 Tab1:** Eligibility criteria in Relay-HC trial

Inclusion criteria	
1. Age > 18 years old and ≤ 80 years old	
2. Diagnosis of hilar cholangiocarcinoma by preoperative imaging and laboratory examination; confirmed as biliary malignant tumor by intraoperative frozen and postoperative pathology; evaluated as resectable by preoperative imaging	
3. Preoperative CT/MRI shows no obvious lymph node metastasis of groups 9, 14 and 16	
4. Child-Turcotte-Pugh A–B grade of liver function	
5. Residual liver volume > 30% 6. ASA grade 1–3	
7. The patient has self-care ability, understands and voluntarily signs the written informed consent, and is able to complete the follow-up plan	
8. Female patients of gestational age must be excluded from pregnancy	
9. The patient has signed the written informed consent form before the screening test	
Exclusion criteria	
1. Tumor R1 resection	
2. The patient has obvious heart, lung, brain, or kidney dysfunction that affects the treatment of cholangiocarcinoma	
3. The patient has a history of other malignancies	
4. Child-Turcotte-Pugh C grade of liver function	
5. ASA grade 4–6	
6. Females who are pregnant or breastfeeding	
7. Patients who are not suitable for the study as determined by the researcher	

The principal analysis consists of an intention-to-treat comparison of the major complications in both groups, using a Mann-Whitney *U* test for ordered categorical data with a two-sided 0.05 significance level. The proportion of patients with any severe operation-related complication will also be expressed in terms of relative risk (RR) and 95% confidence interval (CI). Categorical variables are evaluated using Pearson’s χ^2^ test or Fisher’s exact test.

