**Methods:**

The Relay-HC trial is a prospective, multicenter, and randomized controlled trial. Seven hundred and thirty-four eligible patients with resectable perihilar cholangiocarcinoma across 15 tertiary hospitals in China will be randomly assigned (1:1) to receive either regional lymphadenectomy or extended lymphadenectomy. The primary objective is to determine the overall survival after the two approaches. Secondary objectives of the study include the evaluation of perioperative mortality, postoperative complication, and disease-free survival. This study has been approved by the ethics committee of each participating hospital.

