## Methods

### Design

The Relay-HC trial is a prospective, multicenter, randomized controlled trial. Patients who will receive curative radical resection for hilar cholangiocarcinoma would be randomly assigned (1:1) to receive either regional lymphadenectomy or extended lymphadenectomy. The sample size calculation resulted in a requirement of 734 patients. On the basis of previous data, the median 5-year OS of patients with hilar cholangiocarcinoma who underwent regional lymphadenectomy (P1) was 0.17 (0.07–0.20) [6–9], and the 5-year OS for those with extended lymphadenectomy (P2) was 0.26 [3, 10, 11]. The α level (type I error) is set as 0.05 (one-sided), β is set as 0.2, and the power is set as 0.8. The formula to calculate the sample quantity for a high-quality clinical trial is [12]:
$$ {n}_1={n}_2=\frac{\Big[{u}_a\sqrt{2p\left(1-p\right)}+{u}_{\beta}\sqrt{p_1\left(1-{p}_1\right)+{p}_2\left(1-{p}_2\right)\Big]{}^2}}{{\left({p}_1-{p}_2\right)}^2} $$

The minimum sample size for each group is 330. As the actual sample size includes 10% shedding, the actual sample size of each group is thus 367 patients.

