### Setting

The study is performed at hepatobiliary surgery centers from 15 tertiary hospitals that receive the majority of patients with hilar cholangiocarcinoma from various parts of China. Each of the centers is qualified for standard radical resection of hilar cholangiocarcinoma and regional/extended lymph node dissection. The institutional review board at each hospital has approved the protocol. The number of cases for each center is allocated according to the number of annual cholangiocarcinoma surgeries. A flowchart of the study design was shown in Fig. 1.

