### Randomization

Patients who will receive curative radical resection for hilar cholangiocarcinoma would be randomly assigned (1:1) to regional lymphadenectomy or extended lymphadenectomy by computer-generated allocation based on the envelope method and the hierarchical block randomization method. The envelopes are sealed, opaque, and sequentially numbered. Randomization is performed by the trial coordinator (Study Group of Biliary Surgery of the Surgery Branch of the Chinese Medical Association). The random number table and the block assignment number table will be kept confidential by the full-time secretary of this project. Center-stratified block-permuted randomization is used in this trial. Trial participants are subdivided into strata such as centers; then permuted block randomization is used for each stratum with a block size of 4.

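### Randomization is stratified by center, but the primary overall survival test is described as a univariable log-rank test and no center term is named for the Cox model

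*Protocol article*

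**What the plan says.** The Randomization section of the protocol article states: "Center-stratified block-permuted randomization is used in this trial". It treats centers as the strata, and "then permuted block randomization is used for each stratum with a block size of 4". The abstract places recruitment "across 15 tertiary hospitals in China". The centers will differ in size, because the Setting section says: "The number of cases for each center is allocated according to the number of annual cholangiocarcinoma surgeries".

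For overall survival in the intention-to-treat population, the Statistical analysis section says that "the log-rank test for univariable testing and Cox regression would be used to compare the long-term prognosis" in the two arms. It lists no stratification factor for the log-rank test and no covariates for the Cox model. Center does not appear anywhere in that section.

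**The concern.** Blocks of 4 within center keep the arms nearly equal in every center, so differences in survival between centers add almost nothing to the chance difference between arms. An unstratified log-rank test does not take this into account. Its variance is computed as if arm had been assigned without regard to center, so it is too large when centers differ. The test then rejects less often than its nominal level under the null and loses power under the alternative.

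The Cox model raises a related issue. When an important prognostic factor is left out, the hazard ratio that it estimates is a population-averaged one, nearer 1 than the ratio comparing patients within the same center.

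At stake are the efficiency of the primary comparison and the meaning of its hazard ratio. The stratification is already in place, so the analysis can use it at almost no cost.

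**Working it through.** **1. The plan's own sample size.** The Design section uses 5-year survival of 0.17 (regional) and 0.26 (extended), α 0.05, power 0.80 and a pooled-variance formula for two proportions. With p = 0.215, √(2p(1−p)) = 0.581 and √(p₁(1−p₁) + p₂(1−p₂)) = 0.577:

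- two-sided: (1.960 × 0.581 + 0.842 × 0.577)² / 0.09² = 326, close to the stated 330;
- one-sided, as the section states: (1.645 × 0.581 + 0.842 × 0.577)² / 0.09² = 257, which does not match.

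Dropout: 330 / 0.9 = 367 per group, 734 in total, as stated. The mismatch in sidedness is a separate matter. It is the reason why both levels are shown below.

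**2. Reserve of the log-rank test.** Under proportional hazards, HR = ln 0.26 / ln 0.17 = 0.760. Deaths by 5 years: 330 × (0.83 + 0.74) = 518. Schoenfeld: √(518/4) × |ln 0.760| = 3.12. Power is Φ(3.12 − 1.96) = 87.7% two-sided and Φ(3.12 − 1.645) = 93.0% one-sided, so there is room above 80% before center effects enter.

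**3. Simulation.** There were 3,000 trials per setting, each with 660 patients, 15 centers and blocks of 4 within center. Survival was exponential with 5-year control survival of 0.17 in an average center, a within-center HR of 0.760, and censoring at 5 years. Center effects on the log-hazard were normal. Two inputs are assumptions because the article gives no figure: the SD of the center effects, and center sizes rising evenly in a 1:3 ratio (22 to 66 patients). Each cell gives unstratified / stratified by center.

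| SD | HR | Power, two-sided 0.05 (%) | Power, one-sided 0.05 (%) | Type I error, two-sided (%) |
|---|---|---|---|---|
| 0 | 0.760 / 0.759 | 87.8 / 86.9 | 93.1 / 92.8 | 5.3 / 5.3 |
| 0.2 | 0.763 / 0.759 | 86.5 / 87.2 | 92.1 / 91.9 | 5.2 / 5.6 |
| 0.3 | 0.770 / 0.760 | 85.0 / 86.4 | 91.4 / 92.0 | 4.8 / 5.6 |
| 0.5 | 0.785 / 0.763 | 78.9 / 85.1 | 87.1 / 91.3 | 3.2 / 4.7 |
| 0.7 | 0.799 / 0.759 | 72.2 / 84.3 | 82.6 / 91.0 | 2.4 / 4.7 |
| 1.0 | 0.822 / 0.762 | 59.3 / 82.8 | 72.2 / 89.9 | 1.6 / 4.7 |

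The Monte Carlo standard error is about 0.6 points on power and 0.4 on type I error, so the type I values slightly above 5 are compatible with 5. Under the null the mean HR was about 1.00 for both methods.

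A separate simulation with 15 equal centers of 44 patients (1,500 trials per setting) gave two-sided power of 85 / 87% at SD 0.3, 80 / 86% at 0.5 and 72 / 85% at 0.7. With no center differences it gave 89.2 / 88.5%.

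**4. Which SD is plausible?** The nearest figures in the article are the spread of 5-year survival across published regional series, 0.07 to 0.20. Under exponential survival the log-hazard range is ln(ln 0.07 / ln 0.20) = ln 1.65 = 0.50. If the four citations are four series, the expected range is about 2.06 SD, so SD ≈ 0.50 / 2.06 = 0.24. Adding the 31% series cited in the Discussion, the range is ln(ln 0.07 / ln 0.31) = 0.82. With five series (expected range 2.33 SD), SD ≈ 0.35. These are rough, because differences between studies include sampling error and case mix and are only a proxy for differences between centers.

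**The case against.** The strongest reply is that the article never says the analyses are unadjusted. Univariable may only set the log-rank test apart from the Cox model, the Cox covariates are not listed, and a condensed article commonly leaves strata and covariates to the full protocol or analysis plan. For the Cox model this stands: a reader might infer that center is excluded, but the text is silent. For the log-rank test it stands only in part. The article names the test and calls it univariable, which most naturally means arm alone. Followed as written, it drops the one factor that the design balances.

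A reader might also infer that the primary analysis is biased or its p-value invalid. The documents do not support that. The shift in the hazard ratio is non-collapsibility, meaning that the marginal and within-center ratios are different quantities. Under the null there is no bias, and the type I error is not inflated.

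Finally, the large losses need large center differences. With a typical 5-year survival of 0.17, an SD of 0.5 puts 95% of centers between 0.17^exp(0.98) = 0.9% and 0.17^exp(−0.98) = 51%. An SD of 0.7 gives about 0.1% to 64%. Nothing in the article supports so wide a spread, and its common eligibility criteria, central training and standardized surgery argue against it. The volume-based case allocation shows that centers differ in size, not in survival. This objection stands and limits the size of the point.

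**Conclusion.** The point holds as one of efficiency and clarity. The primary log-rank test as described does not use the center stratification, and the Cox specification leaves center open. If centers differ in survival, the unstratified test is conservative and the unadjusted hazard ratio sits nearer 1 than the within-center ratio.

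The direction is firm; the size is not. At the SD values nearest to the article's own figures (0.2–0.3), the hazard ratio is 0.763–0.770 against 0.760, and about 1 point of two-sided power is lost. At an SD of 0.5 the loss is about 6 points and two-sided power drops just under the planned 80% (78.9%). At 0.7 it is about 12 points.

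It would be wrong to conclude that the trial is underpowered for this reason. At the stated one-sided 0.05, unstratified power is 82.6% even at an SD of 0.7. The figures assume exponential survival, proportional hazards within centers, normal center effects and complete 5-year follow-up of 660 patients. The change is worth making because it is nearly free, not because the planned analysis would mislead.

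**What to change.** In the Statistical analysis section, make three changes:

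- Name the primary overall survival test as a log-rank test stratified by center, in place of the univariable log-rank test.
- State that the Cox model for the hazard ratio and its confidence interval is stratified by center, or uses a center frailty.
- Give a rule for pooling very small centers, fixed before unblinding.

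If a separate analysis plan already stratifies by center, the article's wording should be aligned with it.

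The cost is about 1 point of power or less if centers do not differ (87.8% to 86.9% two-sided with sizes in a 1:3 ratio; 89.2% to 88.5% with equal sizes). That cost was not examined for more uneven centers, which is why the pooling rule is needed. The reported hazard ratio becomes a within-center ratio and should be described as such. Recruitment, data collection and sample size are unaffected.

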### Case selection

All patients aged between 18 and 80 years old with hilar cholangiocarcinoma would be referred for a multidisciplinary team evaluation at each center. Hilar cholangiocarcinoma is defined as a cholangiocarcinoma that develops at the point where the left and right hepatic ducts join to form the common hepatic duct (as determined by computed tomography [CT] imaging or magnetic resonance cholangiopancreatography, or both). Criteria for resectable hilar cholangiocarcinoma include an anticipated complete (R0) resection with adequate future liver remnant (FLR > 30%) and Child-Turcotte-Pugh grade A–B, as well as American Society of Anesthesiologists (ASA) grades I–III. The residual liver volume will be assessed by three-dimensional reconstruction of CT images. These procedures will be accomplished by professional radiographers and the multidisciplinary teams from each center, who will be trained at the leading affiliation to ensure standardization. Patients who also have other malignancies would be excluded from the study.

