### Blinding

Concerning random allocation, a sealed envelope will be issued to the surgeon before the operation by a project secretary. Normally there are two secretaries who are recruited for the clinical trial data management who are not involved in the operation. Then the surgeon unpacks the envelope and performs the operation according to the allocation in the envelope. The patients, outcome assessors, pathologists, and data analysts will not know the grouping information.

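### Table 1 makes achieved margin status and postoperative pathology eligibility criteria, although both are known only after randomization and after the allocated operation

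*Protocol article*

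**What the plan says.** All places are in the protocol article.

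- **Statistical analysis, Table 1.** The first exclusion criterion is "1. Tumor R1 resection". Inclusion criterion 2 requires the tumor to be "confirmed as biliary malignant tumor by intraoperative frozen and postoperative pathology".
- **Case selection.** The resectability rule is prospective: "Criteria for resectable hilar cholangiocarcinoma include an anticipated complete (R0) resection with adequate future liver remnant".
- **Blinding.** On allocation, "a sealed envelope will be issued to the surgeon before the operation by a project secretary". The order of events follows: "Then the surgeon unpacks the envelope and performs the operation according to the allocation in the envelope". Patients, outcome assessors, pathologists and data analysts are to be unaware of the arm. The surgeon is not.
- **Statistical analysis, text.** Overall survival (OS) is compared in the intention-to-treat population. "Time zero is set as the time of randomization", and "all patients who have been randomized would be included in the full analysis set (FAS". The PPS is the subset of "patients who meet the inclusion and exclusion criteria (Table 1), are compliant, and do not violate the clinical trial protocol".
- **Observation indices.** A negative pathological margin, together with at least six lymph nodes, is the sign that the operation did what it was meant to do.

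**The concern.** An eligibility criterion should be decidable when the patient is randomized. Achieved margin status and postoperative pathology are not. Margin status is also a result of the operation being compared, carried out by a surgeon who knows the allocation, and the article uses it elsewhere as an efficacy result.

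Two consequences follow, and they concern different analysis sets.

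1. **Primary OS comparison.** Table 1 calls R1 and non-malignant cases excluded, while the FAS keeps them. The article does not say whether such a patient stays under follow-up for five years or is withdrawn as ineligible, and 15 centers could act differently. If patients are withdrawn on a result of surgery, the groups compared are no longer those formed by randomization.
2. **PPS.** Membership requires meeting Table 1, so this set is selected on a post-randomization result whatever the centers do.

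A third, separate issue is dilution. Patients found unresectable or benign after allocation stay in the FAS but cannot show the effect of the compared dissection.

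**Working it through.** **Step 1. When each item is known**

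| Item | Where | Known at randomization? |
|---|---|---|
| Anticipated R0 | Case selection | Yes |
| Frozen section result | Table 1, inclusion 2 | No, if the envelope is opened before surgery as the Blinding section reads; it could be if opening came later |
| Postoperative pathology | Table 1, inclusion 2 | No, on any reading |
| Achieved margin (R1) | Table 1, exclusion 1 | No, on any reading |

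Opening the envelope later would resolve only the frozen section. The last two rows remain.

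**Step 2. The plan's own sample size**

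Inputs from the Design section: p1 = 0.17, p2 = 0.26, α = 0.05 (stated as one-sided), power 0.8, 330 per group, 10% loss. With p̄ = 0.215, the printed formula is

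n = [u_α √(2p̄(1−p̄)) + u_β √(p1(1−p1) + p2(1−p2))]² / (p1−p2)²

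- Two-sided, u_α = 1.96: (1.1387 + 0.4860)² / 0.0081 = 326, close to the stated 330.
- One-sided, u_α = 1.645: (0.9557 + 0.4860)² / 0.0081 = 257.
- Loss: 330 / 0.9 = 367 per group, 734 in total. This reproduces.

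The stated number fits a two-sided test and the stated α is one-sided. That mismatch is a separate matter, but because of it power is shown both ways below. With all 367 per group evaluable, power for 0.17 against 0.26 is 84% two-sided and 91% one-sided.

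**Step 3. Dilution in the FAS (illustration)**

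The article gives no rate of unresected or benign cases. Assume that a fraction f in each arm is unresected with 5-year OS of 0%. Then each arm's rate is (1−f) times its planned value, and the difference is 9 × (1−f) points.

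| f (assumed) | Rates | Difference | Power, two-sided | Power, one-sided |
|---|---|---|---|---|
| 0 | 0.170 vs 0.260 | 9.0 points | 84% | 91% |
| 10% | 0.153 vs 0.234 | 8.1 points | 79% | 87% |
| 20% | 0.136 vs 0.208 | 7.2 points | 73% | 83% |
| 30% | 0.119 vs 0.182 | 6.3 points | 67% | 77% |

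These figures are for 367 evaluable per group. The 10% allowance replaces lost patients; it does not restore a smaller difference.

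**Step 4. Selection on margin status (illustration, R0-only comparison)**

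Assume no treatment effect, OS of 17% in both arms and R1 survival of 5%. Survival among R0 patients is (0.17 − r × 0.05) / (1 − r), where r is the R1 rate.

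- r = 20% in both arms: 0.160 / 0.80 = 20.0% in each. No artefact.
- r = 20% against 30%: 20.0% against 0.155 / 0.70 = 22.1%, a spurious 2.1 points beside a planned 9.

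In this set-up the artefact appears only if R1 rates differ by arm. It would reach the primary comparison only if R1 patients were withdrawn from it.

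**The case against.** The strongest reply is that the primary set is already settled. OS is compared by intention to treat, from randomization, in all randomized patients, and Table 1 acts as an analysis filter only in the PPS. Keeping eligibility violators in the FAS and dropping them from the PPS is ordinary practice. This largely stands. A reader might infer from Table 1 that R1 patients leave the primary OS analysis, so that it is already biased and short of patients. The text does not support that: nothing in it removes them from the FAS. What remains is that the article names the same patients as excluded without saying that they stay under follow-up, and that the PPS is selected on the achieved margin.

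Other points also have force.

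- **Dilution by R1 patients.** A reader might count R1 patients as diluting the effect. They were resected and can have had the allocated dissection. The article also does not say whether its assumed 0.17 and 0.26 already include R1 cases. Step 3 therefore concerns unresected patients only.
- **Unequal R1 rates.** The Procedure section gives both arms the same liver and bile duct resection and varies only the node stations. It offers no reason to expect the 10-point gap used in Step 4.
- **Timing.** The Blinding section does not place envelope opening relative to exploration or frozen section, and the flowchart is not available. Final margin and postoperative pathology still come after randomization.
- **R1 read as anticipated R1.** The table does not say so, and Case selection shows that the authors write anticipated when they mean it.

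**Conclusion.** The point holds as a defect in the eligibility wording. Two Table 1 criteria depend on results that exist only after randomization and surgery. They conflict with the anticipated R0 rule in Case selection, with the use of a negative margin as an efficacy result, and with a FAS of all randomized patients. The primary OS analysis is exposed only if centers act on Table 1 and withdraw R1 or non-malignant cases, which the text leaves open. The PPS is exposed as written.

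No size can be fixed from the documents. The 79–67% (two-sided) and 87–77% (one-sided) power figures assume 10–30% unresected with no 5-year survivors and 367 evaluable per group. At 10% the two-sided figure is about the planned 80%, and one-sided power falls below 80% only towards the upper end of the range. The 2.1-point artefact assumes both R1 survival and unequal R1 rates. The case for correction rests on the contradiction in the text, not on these figures.

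**What to change.** 1. Delete R1 resection and the postoperative pathology confirmation from Table 1. Use the anticipated R0 criterion of the Case selection section, so that eligibility rests on what is known at randomization.
2. State that every randomized patient, including R1, unresected and non-malignant cases, is followed for OS and stays in the intention-to-treat/FAS primary analysis.
3. Report R1 as an outcome by arm.
4. Do not define the PPS by achieved margin. Label any R0-only analysis as supportive and non-randomized.

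The cost is protocol wording, a notice to the 15 centers, and continued follow-up of patients whom a center might otherwise have withdrawn. Any already withdrawn on these grounds should be identified and, where possible, their survival status obtained.

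Opening the envelope only after exploration and frozen section is an option that would reduce dilution by unresected or benign cases. It is not required. Recruitment began on 30 July 2018, so it would be a mid-trial design change that mixes patients randomized before and after exploration, and it would need a log of consented patients who were not randomized.

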### Observation indices

The primary endpoint will be the 5-year OS rate. The secondary efficacy index includes the primary complication (Clavien-Dindo grades > II) within 30 days postoperatively, perioperative mortality, 6-month OS and DFS, 1-year OS and DFS, 3-year OS and DFS, and 5-year DFS. Cancer-specific survival is determined at the time of cholangiocarcinoma-related death. Disease-free survival is the time to any recurrence. The efficacy evaluation is based on the postoperative pathology: if the postoperative pathological margin is negative and LN ≥ 6, the operation is considered to have achieved the desired purpose. The safety index includes vital signs, adverse events, and clinical laboratory parameters (blood routine, urine routine, myocardial enzymes, coagulation, blood biochemistry, electrocardiogram, cardiac ultrasound), as well as early withdrawal (Fig. 2).

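### A complications test is called the principal analysis although overall survival is primary, and survival is sized as a 5-year rate but tested by log-rank and Cox

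*Protocol article*

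**What the plan says.** All references are to the protocol article.

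- **Objective.** The Methods paragraph of the Abstract states: "The primary objective is to determine the overall survival after the two approaches". The Background says the same and puts complications among the secondary endpoints.
- **Endpoint.** Observation indices: "The primary endpoint will be the 5-year OS rate".
- **Size.** Design compares two 5-year OS proportions, 0.17 (regional) and 0.26 (extended), with a one-sided alpha of 0.05 and power 0.8. It arrives at 330 per group, or 367 after 10% losses.
- **OS analysis.** Statistical analysis: "Concerning the primary endpoint (overall survival), the log-rank test for univariable testing and Cox regression would be used to compare the long-term prognosis", in the intention-to-treat population.
- **Status of complications.** Observation indices: "The secondary efficacy index includes the primary complication (Clavien-Dindo grades > II) within 30 days postoperatively". The secondary list in Statistical analysis also contains "the primary complication within 30 days after surgery (Clavien-Dindo grade > II), and perioperative mortality".
- **Principal analysis.** Later in Statistical analysis: "The principal analysis consists of an intention-to-treat comparison of the major complications in both groups". The test named there is the Mann-Whitney U at a two-sided level of 0.05. Nothing in that sentence limits it to safety or to the secondary endpoints.

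**The concern.** There are two conflicts in the current text.

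The first is one of rank. An outcome that the protocol twice lists as secondary receives the label of principal analysis, and with it the only significance level attached to a named test. The only alpha linked to OS is the one-sided 0.05 in the sample-size paragraph. Complications at 30 days will be known years before 5-year survival, and Design gives no power for them. Taken literally, the label would let the trial be reported on a test for which it was not sized.

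The second concerns the survival question. The endpoint is defined and sized as survival at one time point, but the named methods compare whole survival curves. The two can give different answers when hazards are not proportional. That is plausible here: the experimental arm is the more extensive operation, the Discussion describes added morbidity as a long-standing worry of surgeons, and time zero is randomization, so early surgical deaths count in OS. If the deciding quantity is left open, it can be chosen after the data are seen.

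**Working it through.** **1. Rank of the two outcomes.** OS is primary in four places: Abstract, Background, Observation indices and the opening of Statistical analysis. Complications are secondary in three of these: Background, Observation indices and the opening of Statistical analysis. One later sentence in Statistical analysis makes complications principal. That sentence cannot stand beside the others.

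**2. The protocol's own size.** Inputs from Design: p1 = 0.17, p2 = 0.26, mean p = 0.215, power 0.80. The printed formula is

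n = [u_α √(2p(1−p)) + u_β √(p1(1−p1) + p2(1−p2))]² / (p1−p2)²

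with √(2 × 0.215 × 0.785) = 0.581, √(0.1411 + 0.1924) = 0.577 and (p1−p2)² = 0.0081.

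- One-sided 0.05, as stated: (1.645 × 0.581 + 0.842 × 0.577)² / 0.0081 gives 257 per group, not 330.
- Two-sided 0.05: (1.960 × 0.581 + 0.842 × 0.577)² / 0.0081 gives 326 per group, close to 330.
- Losses: 330 / 0.9 = 367, as stated.

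The stated 330 therefore fits a two-sided alpha better than the one-sided alpha printed beside it. This is a separate matter, but it means that the sidedness of the OS test also has to be settled. With 330 per group the two-proportion test has 80.5% power two-sided and 88.0% one-sided.

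**3. The same assumptions expressed for a log-rank test.** Proportional hazards is an assumption here; the protocol does not state it.

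- Hazard ratio = ln 0.26 / ln 0.17 = 0.760, so |ln HR| = 0.274.
- Deaths for 80% power (Schoenfeld), two-sided 0.05: 4 × (1.960 + 0.842)² / 0.274² = 418 (computed with unrounded values).
- The same, one-sided 0.05: 4 × (1.645 + 0.842)² / 0.274² = 330. This counts total deaths; its match with 330 patients per group is a coincidence.
- Deaths expected by 5 years if 330 per group are all followed: 330 × (0.83 + 0.74) = 518.
- Power with 518 deaths: Φ(√518 / 2 × 0.274 − 1.960) = 0.877 two-sided; with 1.645 in place of 1.960, 0.930 one-sided.

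**4. Why the two OS criteria can differ.** The difference in cumulative hazard at 5 years counts early and late hazard differences equally. The log-rank statistic weights each hazard difference by Y1·Y2/(Y1+Y2), where Y1 and Y2 are the numbers at risk. Per patient randomized in each arm, and without censoring, that weight is 1 × 1 / 2 = 0.50 at the start and 0.17 × 0.26 / 0.43 = 0.103 at 5 years, about a fifth as much. Early excess deaths followed by later benefit would thus pull the log-rank result down more than the 5-year difference. Under proportional hazards this tension disappears, and the log-rank test is the more powerful of the two (88% against 80.5%, two-sided).

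**The case against.** The best defence is that the intention is clear. Four places make OS primary, Statistical analysis ties its test to the primary endpoint by name, and the discordant sentence opens a paragraph otherwise about complications and categorical variables, so a slip in wording is a fair reading. Log-rank with Cox is a conventional pairing of test and estimate, and formal precedence between them is commonly left to a statistical analysis plan. Scheduled follow-up ends at 5 years, so a log-rank comparison can sit beside a headline 5-year rate, and under proportional hazards it costs no power.

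Most of this stands, and it limits the point. It does not remove the contradictory label, which is in the text itself and is not a detail left to a later plan. Nor does it make log-rank or Cox a test of a 5-year proportion.

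A reader might go further and infer that the trial has several independent ways to succeed, with a family-wise error of 9.75% for two tests at 0.05 or 14.3% for three. The documents do not support that. Nowhere do they say that any one of several tests may win. The OS analyses use the same deaths and are strongly correlated. A difference in complications would be a safety signal: the Background hypothesis is better prognosis without more major complications.

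**Conclusion.** The point holds as a conflict of stated rules on two counts: a secondary outcome carries the principal label, and the primary endpoint is defined and sized as a 5-year rate but analysed as a time-to-event comparison. It affects which result decides the trial, so it should be corrected. It does not show that OS lacks a test, since one is named, and no inflation of the type I error can be computed from the text.

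The sample size is not threatened by settling on the log-rank test. About 518 expected deaths exceed both the 418 needed at two-sided 0.05 and the 330 needed at one-sided 0.05. These figures rest on proportional hazards, on the protocol's rates of 0.17 and 0.26, and on 330 patients per group followed for the full 5 years. With early surgical deaths and a later benefit, the 418 and the 88% would not be reliable.

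**What to change.** 1. In Statistical analysis, state that the principal analysis is the intention-to-treat comparison of OS, and relabel the complications comparison as a secondary safety analysis.
2. Align Design, Observation indices and Statistical analysis on one deciding OS test, with one alpha and one sidedness. The simplest choice keeps the present analysis text: the log-rank test decides, the Cox hazard ratio with 95% CI is the estimate, and Kaplan-Meier 5-year OS by arm, with its difference and CI, is supportive. Making the Kaplan-Meier 5-year difference the primary test would resolve the conflict equally well and would match the present endpoint and size basis.
3. If the log-rank test is chosen, name OS as the endpoint in Observation indices and restate the size basis in deaths under proportional hazards (hazard ratio 0.76): 418 at two-sided 0.05, or about 330 at the one-sided 0.05 now in Design, against about 518 expected.

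No extra patients are needed. The cost is a protocol amendment, which under the log-rank option changes the endpoint wording and the size basis and so is more than an editorial correction. The article gives recruitment as having begun on 30 July 2018, so the amendment should be made and dated before outcome data are examined.
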